## Abstract

**Background:**

One in five young children globally suffer the consequences of stunted growth and development and millions experience deficiencies in zinc, iron, iodine, vitamins A and B12, nutrients found bioavailable in fish foods. Small-scale fisheries have the potential to generate income and augment fish consumption while being environmentally sustainable if appropriately managed. However, those engaged in small-scale fisheries are often marginalized, poor, and malnourished. The *Samaki Salama* project seeks to better understand and address these challenges through a three-arm, longitudinal matched cluster study which evaluates the impact of an integrated nutrition social marketing and modified fishing trap intervention.

**Methods:**

There will be 400 small-scale fisher households enrolled from Kilifi County, Kenya and residing in communities matched on location (rural), livelihoods, and child nutritional status. The sample will include mothers and other caregivers, children 6–60 months, and fishers in the family. Applying a cluster design, the matched communities will be divided into three groups: (1) control (*n* = 200); (2) multi-component nutrition social marketing intervention to fishers, mothers, and health workers (*n* = 100); and (3) multi-component nutrition social marketing intervention plus modified fishing traps and training (*n* = 100). Primary outcomes include child growth, fish food intakes, and fisheries yield of mature fish. Secondary outcomes are diet diversity, child diarrheal morbidity, and fisheries revenue. A process evaluation will be used to monitor and ensure fidelity of intervention delivery.

**Discussion:**

This study builds on a growing body of literature illustrating the effectiveness of nutrition focused social marketing campaigns to promote active engagement of participants, high compliance to the intervention, and sustained behavior change. The second intervention element of modified fishing traps that allow immature fish to escape enables participants to act on the messaging they receive and promotes sustainable fishing through increased harvest efficiency and reduced catch of immature fish. The integrated approach of the *Samaki Salama* intervention provides an example of how to leverage multiple disciplines to address key challenges to human and environmental health and illustrates a pathway for scaling study innovations to other small-scale fisheries systems.

**Trial registration:**

https://clinicaltrials.gov (NCT05254444).

## Introduction

Human populations continue to experience nutrient deficiencies with dire health consequences associated with diminishing dietary diversity and a lack of access to certain foods. Stunted growth and development arise from these deficiencies and act synergistically with poverty to reduce the potential of societies to achieve productivity and human wellbeing. Globally, the nutrient deficiencies found widely prevalent – zinc, iron, iodine, vitamins A and B12, among others – are also those found bioavailable in fish foods (1, 2). This speaks to the need to ensure access and more equitable distribution of nutrient-dense foods such as fish across populations. Economic, social, and environmental factors act in tandem to influence access and associated nutrition security. Here we propose a study to test the effects of a multi-component nutrition-sensitive intervention to improve nutrition security along with fisheries sustainability and economic resilience in the first 1,000 days of life and beyond.

Definitions of food security commonly include access, availability, and utilization of nutritious and safe diets year-round (3). Most evidence for nutrition interventions, however, comes from trials testing nutrition-specific interventions or those with direct effects on nutrition such as micronutrient supplementation or fortified foods (4). Consequently, there is a need to build the evidence-base for nutrition-sensitive interventions that target food production and income pathways. Our project embeds nutrition objectives and activities in an intervention to increase sustainable fish production through the provision of modified fishing gear, improve household income, and increase awareness about the importance of fish for maternal and child nutrition. We specifically target small-scale fisher households who are particularly vulnerable to food insecurity and malnutrition and lack the necessary extension support and inputs to increase efficient, sustainable fish production.

Poverty and malnutrition disproportionately affect populations engaged in small-scale food production through fisheries, subsistence agriculture, or livestock production (5). Yet, small-scale production provides the majority of food in developing countries and supports the livelihoods of over 60% of the workforce in this sector (6). Of the small-scale food production sectors, fisheries are a major contributor with more than 50 million men and women employed in the sector (7). However, small-scale fisheries (SSF) are underrepresented in the dialogue around the Blue Economy and have been marginalized by large industrial fisheries, aquaculture ventures serving global markets, establishment of no-take fisheries closures to meet conservation goals, coastal development, foreign tourism, and mineral extraction (8–10). Furthermore, considerations of food and nutrition security have been largely absent from Blue Growth initiatives. Our study positions food supply and nutrition security at the forefront of promoting sustainable SSF systems in Kenya's Blue Economy initiatives through a multifaceted intervention that can be scaled to other systems, including aquaculture.

Food production often comes at the cost of the environment and biodiversity (11–13). Compared with industrial fisheries that tend to target a single species, SSF can be more sustainable and achieve greater outputs per unit effort through the utilization of more passive gear types (traps, gill nets, long lines, etc.) that minimize damage to local ecosystems (14). Small-scale fishers are also more likely to keep and utilize a wide range of the marine species that are caught (14). A more diverse catch spreads out the impact of fishing and reduces the risk of a single species collapse or extinction. However, in contexts where SSF have limited resources and gear options, which reduces the types and number of species fishers are able to catch, the level of fishing effort on local marine ecosystems can become unsustainable and stocks may collapse with concurrent harm to the environment (14–16). The potential for over-exploitation and biodiversity loss highlights the importance integrating marine ecosystem sustainability into interventions targeting small-scale fisher households.

Small-scale fisheries in Kenya are chronically overexploited and fish stocks are dwindling as evidenced by a four-fold decrease in marine catch since the 1980s (17). Efforts to combat declines in SSF production in Kenya have focused on improving the management of fishery resources through the establishment of Beach Management Units (BMU), gear restrictions (e.g., spear gun, beach seine) and no-take fisheries closures (18, 19). The *Samaki Salama* project continues efforts to improve fisheries production in coastal Kenya while also integrating critical dimensions of livelihood sustainability and nutrition security. *Samaki salama* means “fish security” in Kiswahili, the local language, and is used as the project name to highlight the economic, ecological, and nutritional facets of the intervention.

### Logic framework

Figure 1 illustrates the logical framework for our integrated nutrition and fisheries intervention We expect our nutrition social marketing campaign to increase consumption of fish among children under 5 and dietary diversity for households, leading to reduced enteric disease morbidities and reduced stunted growth and development. We anticipate modified fishing traps with escape gaps (to allow immature fish to leave the trap while retaining mature fish) to promote fisheries sustainability and increase fisher income, leading to greater harvest efficiency, improved resilience to environmental change, dietary diversification, and improved nutritional status through both direct consumption and indirect poverty reduction pathways.

**Figure 1 F1:**
[figure not shown]
Logical framework.

## Methods and analysis

### Design

We aim to test the effectiveness of the multi-component *Samaki Salama* intervention as it intersects with nutrition security and fisheries sustainability in Kilifi County, Kenya. Table 1 details the specific aims and hypotheses.

**Table 1 T1:** Study aims and hypotheses.

**Study aims**	**Hypotheses**
1. Determine the effects of a multi-component social marketing campaign to promote fish nutrition, dietary diversity, and food safety on child growth	**Primary** Hypothesis 1: Children in combined intervention groups have increased height-for-age *Z* by 0.2 compared to children in the control Hypothesis 2: Children in combined intervention groups have increased weight-for-age *Z* by 0.10 compared to children in the control Hypothesis 3: Children in combined intervention groups have increased fish food intakes by 100 g compared to children in the control
	**Secondary** Hypothesis 4: Children in combined intervention groups have increased dietary diversity by 1.2 compared to children in the control Hypothesis 5: Children in combined intervention groups have reduced diarrheal morbidity by 5 percentage points compared to children in the control
	**Exploratory** Hypothesis 6: Children in the social marketing + traps intervention group have increased dietary diversity and fish intake compared to children in the social marketing only group
2. Measure the impact of modified fishing traps with escape gaps on catch dynamics and earnings	**Primary** Hypothesis 7: Fishers in the social marketing + traps intervention group have significantly increased fisheries yields of mature fish compared to fishers in the control
	**Secondary** Hypothesis 8: Fishers in the social marketing + traps intervention group will have significantly increased earnings compared to fishers in the control

The intervention will target communities matched based on location (rural), livelihoods, and child nutritional status. The matched sample will be divided into three groups: (1) control (*n* = 200); (2) multi-component nutrition social marketing intervention to fishers, mothers, and health workers (*n* = 100); (3) multi-component nutrition social marketing intervention plus modified fishing traps with escape gaps and training (*n* = 100). Although our original design was to have two comparison groups with equal numbers, formative research showed insufficient numbers of fishers currently using traps that could be recruited to use modified traps. Further, budgetary constraints precluded distributing traps to all 200 in the intervention group. Thus, we split the intervention group enabling us to test the added effects of modified traps together with social marketing. Figure 2 provides an overview of the study design and implementation process.

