“We bring our BMU community”	Social marketing + modified traps	Check in on use of modified traps Refresh knowledge of child nutrition Discuss changes they have noticed in the areas where they fish (environment, fish quantity, fish types etc.) Importance of sharing the information they have received with other fishers Activity to develop a persuasive argument to protect the places where they fish and their children's nutrition Commitment to share what they have learned with new fishers and friends

Fisher training, gear modification, and fishing trap distribution constitute the second piece of the intervention. The use of fishing gears modified to decrease juvenile catch has been shown to lead to greater catch diversity and improve the economic value of fishes (16). Second, fishers can gain a competitive advantage when using new gears by fishing new habitats to catch previously targeted species in novel ways (15). This can reduce the impact of fishing on the environment, and in the case of coastal Kenya, coral reefs. Last, gear modifications have been shown to improve harvest efficiency and promote sustainable fish populations by selecting for mature individuals while at the same time improving fisher revenue (29). Using these rationales, our intervention targets fishers using basket traps and provides them with traps modified with escape gaps so immature fish can escape. Trap distribution will occur at landing sites utilized by participating fishers and at local BMU offices. The fishers will also receive training on how to properly maintain the traps they receive. We hypothesize this type of intervention will reduce fishers' dependence on immature fishes, as well as buffer them from potential market variability (30) and enable them to be more resilient to environmental change (31).

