**Primary outcomes**			
Child growth	Anthropometric measures of height and weight	Length-for-age *Z* score (LAZ) Weight-for-age *Z* score (WAZ) Weight-for-length *Z* score (WLZ)	Baseline, 12 mo.
Fish food intakes	24-h intake survey	Fish food intakes in g	Baseline, 12 mo.
Fisheries yield of mature fish	Fish catch survey at landing sites	Monthly catch per unit effort and fish size distribution	5–10 times per month at randomly stratified days over the course of 12 months

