##### Fisheries yield of mature fish

Trained field enumerators will record fish catches at landing sites (fishery-dependent data). The field team will ask permission to count and weigh a fisher's catch when they return from fishing. Upon consent, the enumerators will identify the fish species or genus level and measure the lengths of a sub-sample of the individuals (*n* = 20). Sampling will occur at least four times per month at randomly stratified days, as determined by the moon phase and considering dominant gear types. Monthly catch per unit effort (CPUE) will be determined as the mean daily catch multiplied by the fishing days per month. We will also evaluate species-specific length-frequency distributions to determine the yield of mature individuals. Sustainable yields will be determined by comparing the initial yields vs. the rate of change of yields for each landing site or BMU, based on average length of catch for given species.

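### No listed hypothesis tests the expected shift away from immature fish, and H7 alone cannot tell selective fishing from a larger overall catch

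*Protocol article*

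**What the plan says.** Three parts of the protocol article bear on this.

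- **What the traps are expected to do.** After Table 4, the Interventions section states: "We hypothesize this type of intervention will reduce fishers' dependence on immature fishes". The Discussion paragraph of the Abstract says that the trap component "promotes sustainable fishing through increased harvest efficiency and reduced catch of immature fish".
- **What is listed for testing.** Table 1 (Design) gives Aim 2 as "Measure the impact of modified fishing traps with escape gaps on catch dynamics and earnings" and lists two hypotheses under it. H7, the primary one, is that fishers in group 3 "have significantly increased fisheries yields of mature fish compared to fishers in the control". H8, the secondary one, reads "Fishers in the social marketing + traps intervention group will have significantly increased earnings compared to fishers in the control". The Design text names the same two fisheries outcomes, and the Analysis section models only fisheries yield and earnings on the fisheries side.
- **What is measured.** Table 5 gives the indicator for the primary fisheries outcome as "Monthly catch per unit effort and fish size distribution". The section on fisheries yield of mature fish has enumerators measure a sub-sample of 20 fish and use "species-specific length-frequency distributions to determine the yield of mature individuals". It defines monthly catch per unit effort as average daily catch times the number of days fished in the month. It also describes a sustainable-yield assessment for each landing site or Beach Management Unit (BMU), based on average length by species.

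**The concern.** The direct effect of an escape gap is on the immature part of the catch. The protocol predicts that effect in words but lists no hypothesis for it. H7 sees only the mature part, so it responds to anything that raises mature landings, including more fishing with no gain in selectivity.

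Two readings of the result are at risk. A positive H7 could be reported in support of sustainable fishing although as many or more immature fish were landed. A null H7 could be reported as a failure of the traps although they released immature fish as intended.

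**Working it through.** The plan has no figure to reproduce here. H7 carries no effect size, and the Sample size section is built on height-for-age. The check has two parts.

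**1. Is immature catch tested anywhere?**

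| Place in the protocol article | Fisheries content | Immature fish? |
|---|---|---|
| Table 1, H7 | Mature yield, group 3 vs control | No |
| Table 1, H8 | Earnings, group 3 vs control | No |
| Design text | Mature yield; income and earnings | No |
| Table 5 | Monthly catch per unit effort; size distribution | Data only, no contrast |
| Fisheries yield section | Length-frequencies, used for mature yield | Data only, no contrast |
| Same section, sustainable yields | Average length per site or BMU | No hypothesis, group contrast or criterion |
| Analysis | Fisheries yield; earnings | No |

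**2. How does H7 respond to different changes in the catch?**

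The documents give no mature/immature split, so I assume a baseline of M0 = 60 mature and I0 = 40 immature units.

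- Change seen by H7 = M1 − M0
- Immature share = I / (M + I); at baseline 40/100 = 40%

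| Scenario | Mature | Immature | H7 change | Immature share after |
|---|---|---|---|---|
| (a) all catch +25% | 60 × 1.25 = 75 | 40 × 1.25 = 50 | +15 | 50/125 = 40% |
| (b) mature +10%, immature +50% | 60 × 1.10 = 66 | 40 × 1.50 = 60 | +6 | 60/126 = 47.6% |
| (c) mature unchanged, immature −40% | 60 | 40 × 0.60 = 24 | 0 | 24/84 = 28.6% |
| (d) mature +10%, immature −40% | 66 | 24 | +6 | 24/90 = 26.7% |

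Scenarios (b) and (d) give the same value on H7 and opposite results for immature fish. Scenario (c) is the effect expected from the escape gaps, and H7 shows nothing.

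**Does the assumed split matter?** With p the baseline immature share:

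- The share after (b) is 1.5p / (1.5p + 1.1(1 − p)). For p = 0.2 this is 0.30/1.18 = 25.4%; for p = 0.6 it is 0.90/1.34 = 67.2%.
- The share after (c) is 0.6p / (0.6p + 1 − p). For p = 0.2 this is 0.12/0.92 = 13.0%; for p = 0.6 it is 0.36/0.76 = 47.4%.
- Under (a) the share stays at p.

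The directions do not depend on the split.

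**Effect of the monthly scale.** Because the monthly figure is daily catch times days fished, extra days alone raise it. Assume 6 mature and 4 immature units per day over 10 days, with one trip a day: 60 and 40 per month. With 30% more days, 13 in all, this becomes 6 × 13 = 78 and 4 × 13 = 52. H7 moves by +18 and monthly immature landings by +12. Immature catch per trip stays at 4 and the immature share at 40%. Neither a per-trip measure nor the share alone would show the extra immature landings.

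**The case against.** The strongest reply is that the information is already there. Size distribution is part of the primary fisheries indicator in Table 5, classifying fish as mature also classifies the rest as immature, and average length per site feeds a sustainability assessment. In scenario (c) both size distribution and average length would shift. Mature yield is also a legitimate headline outcome for a project about food supply and income, and a condensed article may leave secondary contrasts to a fuller document.

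Much of this stands, and it rules out some stronger readings.

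- A reader might infer that the trial can neither confirm nor refute its trap hypothesis. That goes too far: the data for a test are collected. What is missing is a listed hypothesis and a group contrast.
- A reader might infer that the protocol will treat a positive H7 as proof of sustainable fishing. No passage sets such a rule. Aim 2 speaks of catch dynamics and earnings, and the Abstract gives sustainability as rationale.
- A reader might infer a stated hypothesis that the gaps cut the catch of immature fish. The Interventions section hypothesises less dependence on immature fish; reduced catch is the Abstract's wording, and it is not framed there as a hypothesis.

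The reply does not remove the point. The length-frequencies are assigned to deriving mature yield. The average-length assessment is made by site or BMU, with no comparison of groups and no criterion, and a proportional rise in catch as in (a) leaves average length unchanged. Nor is this a detail deferred to another document: the article says Table 1 sets out its hypotheses, and one hypothesis stated in its own text is not among them.

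**Conclusion.** The point holds as a mismatch between a hypothesis stated in the text and the list of hypotheses to be tested. As written, H7 cannot separate selective fishing from a larger overall catch, and the definition of monthly catch per unit effort adds to this because it rises with days fished. In the illustration, H7 moves by +15 while immature landings rise by 10, and by 0 while they fall by 16.

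The sizes rest on an assumed 60/40 catch and assumed percentage changes; only the directions are general. They show movement of the estimate, not statistical significance, and they do not predict what group 3 will do. The change is worth making because it is cheap and lets the trial test an effect that it states it expects.

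**What to change.** Add to Tables 1 and 5 a secondary hypothesis under Aim 2, group 3 versus control and analysed in the same way as H7, on two measures:

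- (a) the immature share of the catch;
- (b) immature catch on the same monthly scale as H7, not only per trip, because extra trips would otherwise go unnoticed.

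Use the existing length records with the same maturity classification and the same scaling from the 20-fish sub-sample that H7 needs. Name the comparison explicitly as group 3 versus control: the Analysis section pools the two intervention groups for everything except earnings and the exploratory comparison, which does not match H7 in Table 1.

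Report both measures with confidence intervals beside H7, and do not describe a positive H7 on its own as evidence of more sustainable fishing. A rule that accepts H7 as a sustainable gain if immature catch per trip has not risen should not be used: extra trips pass it, and so does a noisy null result.

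The cost is a row in each table, the extra modelling, and one more secondary test. No new fieldwork is needed. Maturity cut-offs for fish identified only to genus, and scaling up from the sub-sample, take work, but H7 already requires both.

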**Figure 2 F2:**
[figure not shown]
Study design.

Both process and impact evaluations will be carried out using mixed methods. Primary and secondary nutrition outcomes include longitudinal difference-in-difference analyses of parameters – height-for-age *Z* score, stunting prevalence, child fish food intake, child dietary diversity, and child diarrheal morbidity. Other outcomes include awareness of the social marketing campaign and knowledge transfer. Primary and secondary fisheries outcomes will be longitudinal difference-in-difference analyses in fisheries yield of mature fish and fisher income and earnings.

The *Samaki Salama* intervention precludes randomization due to the high risk of spill-over effects and the limited number of trap fishers with children under the age of 5. Thus, for the impact assessment, we will conduct a matched intervention/control design to minimize selection bias and test effectiveness on nutrition and fisheries production. Steps have been taken to reduce the risk of selection bias that might arise from the matched design. A pilot study and additional formative research will be used to identify and match communities on important characteristics [socioeconomic status (SES), child nutrition, livelihoods, etc.]. This preliminary data provides additional information needed for external validity and extrapolation of findings to other small fisher households in Kenya and internationally. The longitudinal difference-in-difference design further contributes to the internal validity, accounting for residual confounding, and increases the statistical power to detect intervention effects.

